#### 2.6.3. Development of Educational Materials and Program Validation

The educational materials were developed separately for instructors and participants (tailored to older adults). The teaching materials include standardized teaching guides detailing learning objectives, lecture tips, and important points, along with PowerPoint slides, a manual, weekly handouts, and activity sheets. The learning materials were designed to align with the particularities of older adults, using large fonts, accent colors, and illustrations to improve readability and comprehension. To reinforce learning, videos were created for each of the six injury areas, covering case studies, educational content, and experiential activities.

The completed program and materials were validated by an expert panel consisting of four physicians (specialists in emergency medicine, orthopedics, neurosurgery, and rehabilitation medicine), two professors of geriatric nursing, one exercise specialist, one occupational therapist, and one physiotherapist. After explaining the program’s objectives, the panel evaluated the content, methodology, and feasibility of on-site application. With all items scoring 4 or higher out of 5, the program’s validity was established.

### 2.7. Procedures

Participants who provide consent will undergo eligibility screening, including general characteristics (age, sex, comorbidities) and the K-FRAIL and Mini-Cog tests. Thereafter, eligible participants will be assessed at baseline for demographic characteristics, number of unintentional home injuries over the past 6 months, risk factors, preventive activities, beliefs, psychological health, physical function (grip strength, timed up-and-go test, and one-leg standing test), and health-related quality of life. Randomization will be performed after the baseline assessments. The intervention will span 4 weeks, with the planned programs delivered to the intervention and control groups. Although the frequency of sessions differed between groups (twice per week for the intervention group and once per week for the control group), the total intervention period was identical (4 weeks). The higher session frequency in the intervention group reflects the inclusion of both educational and behavioral components, which required additional sessions for practice and feedback. The control group received lecture-based education only. To minimize potential attention bias associated with different contact times, both groups received comparable educational content, and follow-up monitoring was implemented at similar intervals throughout the study period. Post-intervention assessments will be conducted 1 week and 1 month after program completion at a designated location.

#### 2.7.1. The Intervention Group

Participants in the intervention group will participate in the SHIPs intervention, which integrates lectures, discussions, and experiential activities over 4 weeks. The program consists of eight sessions (two per week), each lasting 60–70 min. The sessions will be conducted in accessible locations, such as senior welfare center classrooms, with small groups of approximately 10 participants. Lectures and discussions will be led by the researcher, and experiential activities will be facilitated with support from a research assistant.

Program adherence will be evaluated by tracking attendance, compliance with home exercises, results from functional ability tests, and the number and percentage (95% confidence interval) of participants who complete the questionnaire assessments. Attendance compliance will be defined as attending 80% or more of the weekly group education and exercise sessions and participating in at least five sessions.

#### 2.7.2. The Control Group

The control group will receive lecture-based education, using the same booklets, videos, and picture quizzes as the intervention group but without the inclusion of discussion components. Sessions will be held in senior welfare center classrooms, with no restriction on the number of participants per group. The lectures will be delivered by the researcher. Pre- and post-assessment methods and procedures will be the same as those used in the intervention group.

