#### 2.6.2. Educational Content and Teaching Methods

The program curriculum was developed based on literature reviews and statistical data [15,25,26,27,28,29,30,31,32,33], prioritizing six important areas of prevention and management at home: fall prevention, cut and collision prevention, burn and fire prevention, swallowing disorder management, medication management, and dehydration/heat-related illness prevention. The teaching methodology was designed to account for the cognitive and social characteristics of older adults, maximizing educational effectiveness by combining lecture-based and discussion-based approaches with demonstrations and hands-on practice.

The program consists of eight sessions, each lasting 60–70 min, divided into four lecture and discussion sessions and four experiential activity sessions [19,34]. The specific details of each session are outlined in Table 1. Lecture-based teaching methods were employed to systematically and effectively deliver a large volume of educational content to multiple participants in a short period [35].

During the lecture sessions (1st, 3rd, 5th, and 7th sessions), participants first watch case-based animated videos illustrating injury mechanisms in the six focus areas, providing foundational knowledge about home safety and encouraging preventive behaviors. After the videos, presentations are used to expand on topics such as injury risk factors and coping strategies. Each lecture concludes with participants completing picture quizzes and receiving small rewards to reinforce key messages, boost motivation, and enhance learning outcomes.

In the discussion sessions (3rd, 5th, and 7th sessions), participants share their experiences with implementing preventive actions to avoid injuries. Real-life testimonials from peers are incorporated to foster self-efficacy and promote the exchange of ideas. While instructor involvement is kept to a minimum, corrective guidance on preventive behaviors is provided through questions and answers to ensure meaningful and productive discussions.

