The program incorporates exercises and hands-on activities to provide participants with opportunities to learn and practice home safety, injury prevention behaviors, and coping strategies. To promote practical behavioral change, experiential activities are included in the 2nd, 4th, 6th, and 8th sessions. These sessions feature fall prevention exercises (2nd session), wound disinfection and hand hygiene practice (4th session), swallowing disorder prevention exercises and first aid training, including the Heimlich maneuver (6th session), and activities focused on proper hydration and medication management (8th session). These activities are designed to help participants apply preventive behaviors effectively in their daily lives.

The fall prevention exercises were adapted from a previous study [29] and structured into beginner and intermediate levels to encourage older adults at risk of frailty or with mild mobility restrictions. The exercises, which can be performed daily at home, include functional and chair-based exercises such as marching in place, walking between rooms, wall push-ups, leg lifting and tapping, seated walking, standing up from a chair, arm stretching, calf stretches, and hamstring stretches. Each session includes group exercises, and participants are encouraged to continue these exercises individually at home at least twice a week. A previous study [36] reported that these exercises improve mobility, walking scores, and balance confidence. Participants are asked to track their home exercises and any unintentional injuries on a sticker chart, which they submit during group training sessions for monitoring and feedback purposes.

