## Figures and Tables

**Figure 1 healthcare-13-02695-f001:**
[figure not shown]
Flow diagram of study design.

**Table 1 healthcare-13-02695-t001:** Composition of the safety and home injury prevention program.

Section	Week		Key Concept	Activity
Fall prevention at home	1	Perceived Susceptibility	Risk factors for falls	Risk factor checklist Watching case-based videos Lecture (video, summary)
		Perceived Severity	Consequences of falls and their impact on quality of life	
		Benefits	Effectiveness of preventive activities	Sharing injury and prevention experiences Preventive activity checklist
		Barriers	Overcoming barriers to falls and coping strategies	
	2	Self-Efficacy	Identifying appropriate preventive actions Home-based fall prevention exercises (beginner level)	Picture quiz Exercise (video, demonstration, workout)
Cut and collision prevention at home	3	Perceived Susceptibility	Risk factors for cuts and collisions	Risk factor checklist Watching case-based videos Lecture (video, summary)
		Perceived Severity	Consequences of cuts and collisions	
		Benefits	Effectiveness of preventive activities	Sharing injury and prevention experiences Preventive activity checklist
		Barriers	Overcoming barriers to cuts and collisions and coping strategies	
		Self-Efficacy	Identifying appropriate preventive actions	Picture quiz
Burn and fire prevention at home	4	Perceived Susceptibility	Risk factors for burns and fires	Risk factor checklist Watching case-based videos Lecture (video, summary)
		Perceived Severity	Consequences of burns and fires	
		Benefits	Effectiveness of preventive activities	Sharing injury and prevention experiences Preventive activity checklist
		Barriers	Overcoming barriers to burns and fires and coping strategies	
		Self-Efficacy	Wound disinfection management	Wound disinfection (video, demonstration, hands-on practice)
Swallowing disorder management at home	5	Perceived Susceptibility	Risk factors for swallowing disorders	Risk factor checklist Watching case-based videos Lecture (video, summary)
		Perceived Severity	Consequences of swallowing disorders and their impact on quality of life	
		Benefits	Effectiveness of self-management activities	Sharing injury and prevention experiences Preventive activity checklist
		Barriers	Overcoming barriers to swallowing disorder management and coping strategies	

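### Section 1.2 states the hypothesis against usual care, but the control arm receives lectures; a minor second point is that Table 1 and section 2.6.2 give different session schedules

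*Protocol article*

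**What the plan says.** **Comparator.** Section 1.2 contains the only research hypothesis. It predicts a larger fall in the home injury count with SHIPs than with usual care. The Abstract and section 2.5 give the control group four lecture-only sessions. Section 2.7 has the control group meeting once a week for four weeks for lecture-based education, with content described as comparable between groups. Section 2.7.2 says the lectures are delivered "using the same booklets, videos, and picture quizzes as the intervention group but without the inclusion of discussion components".

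**Schedule of the intervention.** Section 2.6.2 says: "During the lecture sessions (1st, 3rd, 5th, and 7th sessions), participants first watch case-based animated videos illustrating injury mechanisms in the six focus areas". It names sessions 3, 5 and 7 as the discussion sessions. It adds that "experiential activities are included in the 2nd, 4th, 6th, and 8th sessions", with "activities focused on proper hydration and medication management (8th session") last. Table 1, which sets out the composition of the same program, numbers its units 1 to 8 under a column headed Week. It gives a lecture block to several even-numbered units, for example unit 4, "Burn and fire prevention at home".

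**The concern.** A hypothesis fixes what the primary result may be said to show. Here it names a comparator that the design does not contain. If lectures alone reduce injuries, both arms may improve and the difference between them may be small. A reader who goes by section 1.2 would then take a null result to mean that SHIPs does no better than usual care, a question the trial does not ask. A positive result would also be mislabelled, because it would show a gain over lectures.

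The schedule conflict matters less. Discussion and hands-on practice are what separate the arms, so the description of the intervention should say consistently when they take place. As written, someone delivering or replicating the program from Table 1 would run it differently from someone following section 2.6.2.

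**Working it through.** No sample size or power figure bears on this point. The check is to set the statements side by side and count.

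**1. Comparator**

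| Place | What controls receive |
|---|---|
| 1.2 | usual care |
| Abstract | four lecture-only sessions |
| 2.5 | four lecture-only sessions |
| 2.7 | lecture-based education, once a week for 4 weeks (1 × 4 = 4 sessions) |
| 2.7.2 | lectures with the same booklets, videos and quizzes, no discussion |

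Four of the five places agree with each other, and 1.2 stands alone. Arms receiving usual care: 0 of 2.

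Let U, L and S be the expected injury counts under usual care, lectures only and SHIPs.

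- Section 1.2 concerns U − S = (U − L) + (L − S).
- The two randomized arms estimate L − S.
- U − L, the effect of the lectures themselves, has no randomized estimate in this trial, so U − S has none either.
- Change from baseline in the control arm cannot stand in for U − L. There is no concurrent untreated group, and section 2.8.1 counts injuries over 6 months at baseline but over 1 month at each later assessment.
- L − S is the effect of a package. Intervention participants attend 2 × 4 = 8 sessions and controls 4, so the effects of discussion, practice and extra contact are not separated.

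**2. Schedule**

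The program lasts 4 weeks with two sessions a week (2.7.1), so units numbered 1 to 8 cannot be weeks. They are best read as sessions: falls exercise in 2, wound disinfection in 4, swallowing exercise in 6 and hydration in 8 all match section 2.6.2.

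| Component | Section 2.6.2 | Table 1 | Table 1 entries in the sessions 2.6.2 names |
|---|---|---|---|
| Lecture | 1, 3, 5, 7 | 1 falls, 3 cuts and collisions, 4 burns and fires, 5 swallowing, 7 medication, 8 dehydration and heat | 4 of 6 (outside: 4, 8) |
| Discussion or sharing of experiences | 3, 5, 7 | 1, 3, 4, 5, 7, 8 | 3 of 6 (outside: 1, 4, 8) |
| Hands-on medication practice | 8 | 7 | 0 of 1 |

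Quiz placement also seems to differ. Section 2.6.2 says "Each lecture concludes with participants completing picture quizzes", while Table 1 pairs the falls quiz with the exercise in unit 2. That depends on how merged cells were read from the table, so nothing rests on it here.

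**The case against.** **On the comparator.** The strongest reply is that usual care is a single loose phrase, corrected by every operative section, and that a reader of the Abstract would not be misled. Much of this stands: the contrast actually planned is clear from 2.5, 2.7 and 2.7.2, and randomization, outcomes and analysis are unaffected. But the phrase sits in the only hypothesis, and nothing in the article defines lectures as usual care. The statement is wrong as written.

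**On the schedule.** Table 1 describes the intervention arm and was read by machine, so some misalignment could be an artefact. That is unlikely for the lecture units, because the numbers run 1 to 8 in order and the practical activities match the text. For session 1 there is some slack: section 2.6.2 also speaks of four combined lecture and discussion sessions, although it lists discussion in only three.

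**A stronger reading that does not hold.** A reader might infer that the four control lectures copy Table 1 units 1, 3, 5 and 7, so that controls hear nothing on burns and fires or on dehydration and heat, although the primary outcome counts all six injury types. The article does not support this. No section builds the control lectures from those units, and the inference joins the session numbers of one source to the contents of the other. What bears on control content points to all six topics: section 2.6.2 has the lecture sessions covering six areas, section 2.6.3 says "videos were created for each of the six injury areas, covering case studies, educational content, and experiential activities", section 2.7 calls the content comparable, and section 2.7.2 gives controls the same materials. A topic-by-session list for controls is detail that an article may leave to the full protocol.

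**Conclusion.** The comparator in section 1.2 is wrong as written. The trial tests the full program against lecture-only education and cannot support a conclusion, positive or null, about SHIPs against usual care. The mismatch is complete (0 of 2 arms), and it lies in the stated hypothesis rather than in the conduct of the trial. The conclusion assumes only that controls receive what the Abstract and sections 2.5, 2.7 and 2.7.2 describe. How far the lectures themselves reduce injuries is not given, so no size can be put on the gap between the two contrasts.

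The disagreement between section 2.6.2 and Table 1 is real but minor: two lecture blocks, three experience-sharing entries and the medication practice are placed differently. It rests on reading the Week column as sessions. Nothing shows which schedule is the true one, and no omission of topics from the control arm is shown.

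**What to change.** 1. In section 1.2, replace usual care with lecture-only education using the same materials.
2. Word the conclusion, including any null result, as the added effect of discussion and hands-on practice, together with their extra sessions, over lectures. Make no claim against usual care.
3. Reconcile Table 1 and section 2.6.2 on lectures, discussion and medication practice, following the schedule actually delivered. Neither source should be made to follow the other by default: the planned start was 1 April 2025 (section 3), and parts of 2.5 and 2.7 are already in the past tense, so sessions may have been run.
4. Head the Table 1 column Session.

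Cost: one phrase in 1.2, a constraint on how the result is worded, and edits to a few rows of Table 1 or a few sentences of 2.6.2. No participants, sessions or staff are added, and randomization, outcomes, analysis and sample size stay as they are. The price is a narrower claim: the report can speak about the gain over lectures only.

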### 2.8. Outcomes Measures

#### 2.8.1. Primary Outcome Variables

The number of unintentional home injuries, including falls, cuts/collisions, burns/fires, medication-related incidents, swallowing disorders, and dehydration/heat-related illnesses, will be recorded. At baseline, the number of incidents occurring over the past 6 months will be assessed, whereas at 1 week and 1 month after the intervention, the number of incidents from the preceding month will be evaluated.

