### 1.1. Aims

#### 1.1.1. Primary Objectives

To evaluate the effectiveness of a Health Belief Model (HBM)-based health education program on the number of unintentional home injuries among community-dwelling older adults from baseline to post-intervention and at one-month follow-up.

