	6	Self-Efficacy	Identifying appropriate self-management activities Swallowing disorder prevention exercises	Picture quiz Exercise (video, demonstration, workout), First aid (video, demonstration, hands-on practice)
Medication management at home	7	Perceived Susceptibility	Risk factors for medication misuse and addiction	Risk factor checklist Watching case-based videos Lecture (video, summary)
		Perceived Severity	Consequences of medication misuse and addiction	
		Benefits	Effectiveness of self-management activities	Sharing injury and prevention experiences Preventive activity checklist
		Barriers	Overcoming barriers to medication management and coping strategies	
		Self-Efficacy	Identifying appropriate self-management activities Medication storage and measurement methods	Picture quiz Medication storage and measurement methods (video, demonstration, hands-on practice)
Dehydration and heat-related illness prevention at home	8	Perceived Susceptibility	Risk factors for dehydration and heat-related illness	Risk factor checklist Watching case-based videos Lecture (video, summary)
		Perceived Severity	Consequences of dehydration and heat-related illness	
		Benefits	Effectiveness of self-management activities	Sharing injury and prevention experiences, Preventive activity checklist
		Barriers	Overcoming barriers to dehydration management and coping strategies	
		Self-Efficacy	Identifying appropriate preventive activities Healthy water drinking	Picture quiz Healthy water drinking (video, demonstration, hands-on practice)

**Table 2 healthcare-13-02695-t002:** Schedule of safety and home injury prevention program.

Study Protocol					Closing
	Enrollment	Allocation	Intervention (4 Weeks)	Post- Allocation (5 Weeks)	Post- Allocation (1 Month)
Timeline	Tx	T0	-	T1	T2
Enrollment					
Eligibility screening	X				
Informed consent	X				
Allocation		X			
Interventions: Safety and home injury prevention program					
Intervention group (twice a week)		X	X	X	X
Control group (once a week)		X	X	X	X
Assessments					
Mini-cog test		X			
K-FRAIL scale		X			
Age/sex		X			
Acute illnesses		X			
Fracture		X			
ADL		X			
Balance impairment		X			
Cerebrovascular disease		X			
Active severe pain		X			
Participate in other exercises		X			
Measures					
Number of unintentional home injuries		X	X	X	X
Home injury risk assessment		X	X	X	X
Home injury prevention behaviors		X		X	X
Beliefs about safety and injury prevention behaviors		X		X	X
Psychological health					
Depression		X		X	X

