Fear of falling		X		X	X
Physiological function					
Grip strength		X		X	X
Time up and go test		X		X	X
One-leg standing test		X		X	X
Health-related quality of life		X		X	X

Note: Tx = enrollment; T0 = baseline; T1 = 1week after intervention; T2 = 1 month after intervention; K-FRAIL scale = Korean version of the FRAIL scale; ADL = Activities of Daily Living.

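### The T1 injury count is labelled post-intervention, but about three quarters of its window lies inside the programme and it shares 7 days with the T2 window

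*Protocol article*

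**What the plan says.** The primary objective (section 1.1.1) is the effect on home injuries "from baseline to post-intervention and at one-month follow-up"; the hypothesis in section 1.2 uses the same two follow-up labels. The timings are in section 2.7: "The intervention will span 4 weeks, with the planned programs delivered to the intervention and control groups", and "Post-intervention assessments will be conducted 1 week and 1 month after program completion at a designated location". The note to Table 2 agrees: "T1 = 1week after intervention; T2 = 1 month after intervention". The T1 column of that table is headed "Post- Allocation (5 Weeks" and so on, which is 4 weeks of programme plus 1 week.

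Section 2.8.1 sets the recall periods. At T1 and T2: "whereas at 1 week and 1 month after the intervention, the number of incidents from the preceding month will be evaluated". The 6-month baseline period plays no part in this point.

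Section 2.9 enters T0, T1 and T2 as three time points in a repeated measures analysis of variance, or in generalized estimating equations (GEE) when the data are not normal. Table 2 also marks an injury count in the 4-week intervention column, but section 2.8.1 gives that count no recall period and section 2.9 gives it no analysis. Injury logs are encouraged as a guard against recall bias (Discussion). No rule dates each injury or assigns it to one visit.

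**The concern.** A recall period of one month, asked one week after a four-week programme, reaches back over most of the programme. The T1 count therefore mixes two periods that the objective means to keep apart. T2 looks back one month from one month after the programme, so its window begins where the programme ends and takes in the same first week that T1 has already covered.

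What is at stake is interpretation. The T1 count does not measure the period that the objective names. Two of the three repeated measures contain some of the same events, so the T1-to-T2 change and the group-by-time interaction cannot be read as programme end against follow-up. If the effect builds up during the programme, the T1 contrast also understates the effect reached by its end, in a trial of only 54 people.

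**Working it through.** **Inputs.** Programme of 4 weeks = 28 days (section 2.7); T1 one week and T2 one month after completion (sections 2.7 and 2.8.1, note to Table 2); recall of one month at each (section 2.8.1). The article does not define a month in days, so I take M = 28 to 31 days.

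**The plan's own figure.** T1 after allocation = 4 + 1 = 5 weeks, which matches the Table 2 column. Table 2 heads T2 as 1 month post-allocation, but its own note and sections 2.7 and 2.8.1 place T2 one month after the intervention. I use that.

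**Windows.** Put completion at day 0 and the programme at day -28 to day 0. The T1 window is 7 - M to 7. The T2 window is 0 to M. They share days 0 to 7. The in-programme share of T1 is (M - 7)/M.

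| Month (days) | T1 window | T2 window | Shared days (share of each window) | T1 in programme |
|---|---|---|---|---|
| 28 | -21 to +7 | 0 to +28 | 7 (25.0%) | 21/28 = 75.0% |
| 30 | -23 to +7 | 0 to +30 | 7 (23.3%) | 23/30 = 76.7% |
| 31 | -24 to +7 | 0 to +31 | 7 (22.6%) | 24/31 = 77.4% |

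The overlap is 7 days for every month length. None of the T2 window falls in the programme. If T2 were instead one month after T1, which is not what the text says, the overlap would vanish but the in-programme share of T1 would not change.

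**What the T1-to-T2 change measures.** The shared week cancels: T2 - T1 = injuries on days 7 to M, minus injuries on days 7 - M to 0. The change compares the last 21 to 24 days of the programme with the last 21 to 24 days before T2. With independent injuries at a constant rate (Poisson, assumed), the shared week alone gives a T1-T2 correlation of 7/M = 0.23 to 0.25.

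**Possible dilution at T1.** Assume a final rate ratio of 0.50 and M = 30.44 days. The in-programme share is 23.44/30.44 = 0.770 and the remainder is 0.230. The T1 window opens on programme day 28 - 23.44 = 4.56.

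- Full effect from the first session: T1 rate ratio = 0.50.
- Linear build-up over 28 days: the midpoint of the in-programme part is (4.56 + 28)/2 = 16.28 days, so the mean ratio there is 1 - 0.5 × 16.28/28 = 0.709. T1 rate ratio = 0.770 × 0.709 + 0.230 × 0.50 = 0.66.
- Effect only at completion: 0.770 × 1 + 0.230 × 0.50 = 0.885.

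**The case against.** Four stronger readings are tempting, and the document supports none of them.

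- *Injuries are double counted, so totals are inflated.* Section 2.9 compares the time points and nowhere adds T1 to T2. The shared events add correlation, which repeated-measures methods are meant to accommodate.
- *The treatment comparison is biased.* Section 2.7.2 gives the control group the same assessment methods and procedures, so both arms have the same windows. The randomised contrast at T1 is valid for the mixed period that it covers.
- *T1 mostly reflects time before the content was delivered.* Section 2.6.2 delivers content from the first session, and the fall-prevention exercises come in the second. The T1 window opens only after the first 4 to 7 programme days (28 minus 24 to 21). Programme time is exposed time, so the 0.885 figure is the unfavourable end of a range.
- *The first programme days are lost.* They fall outside the two recall questions, but Table 2 marks an injury count during the intervention, and section 2.12 asks participants to report home injuries at once.

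It is also fair to say that T2 already gives a clean post-programme month. All this limits the consequence. It does not make T1 a post-intervention count, and it does not assign an injury in the shared week to one visit.

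**Conclusion.** The point holds as a fault in how the primary outcome is defined over time. On the article's own timings, 75 to 77% of the T1 window is programme time and exactly 7 days are shared with T2. Neither result depends on the length of a month within 28 to 31 days. The T1 count is therefore not the post-intervention count named in sections 1.1.1 and 1.2, and the T1-to-T2 change and the time interaction are hard to interpret.

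Dilution at T1 is possible but of unknown size. With an assumed final rate ratio of 0.50, it runs from none (0.50) through about 0.66 to about 0.885, depending on when the effect begins, which the article does not state. Because the randomised comparison is unbiased, no total is inflated and T2 is intact, this is a should-fix.

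**What to change.** In section 2.8.1, make the windows non-overlapping by splitting the recall question at the last session, which closes the common 4-week period in both arms:

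- At T1, ask separately for injuries from the first to the last session and for injuries since the last session.
- At T2, ask for injuries since the T1 visit.
- Count each injury once. Take last session to T2 as the primary post-programme count and report the programme period separately.
- Use log(days) as offset. This needs a log-link count model, which the GEE in section 2.9 can supply and the repeated measures analysis of variance cannot.
- Say how the intervention-period injury count marked in Table 2 relates to the first T1 question, so that the two do not overlap in turn.

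Simply asking at T1 about the time since baseline would not do. It would leave T1 at least 4/5 = 80% programme time if baseline falls at programme start, and would add pre-programme time if baseline is earlier.

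The cost is slightly longer forms and windows of unequal length, which the offset handles.
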